### Ethical and safety issues

The trial has received ethics committee approval from the National Research Ethics Service Committee East of England - Cambridge East (Research Ethics Committee (REC) reference 11/EE/0538). It is important to note that the features used to ensure the safety of donors in routine blood donation in NHSBT are being used to ensure the safety of donors in the INTERVAL trial.

The role of the trial’s Independent Data Monitoring Committee is to provide independent advice, based on un-blinded analysis of data, to the Trial Steering Committee in order to ensure the safety of the participants. Hence, at least every 6 months, the trial’s Independent Data Monitoring Committee reviews un-blinded safety data provided by the trial’s independent statistician. These results derive from the various sources described above, including the SF-12v2 questionnaire data and the self-reported adverse events questionnaire.

An increase in deferrals or adverse events compared to habitual donation patterns may prompt participants to request withdrawal from the trial. Participants are free to withdraw from the trial at any time without giving reasons. However, in order to maintain maximal data capture participants are asked to continue to complete the trial questionnaires without donating blood. If participants still wish to withdraw from the trial, then they are given the option to allow permission to the research team to retain and use data already collected from them. Participants are free to opt out of this permission.

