Only participants who returned the baseline questionnaire were eligible for randomisation. After randomisation, participants were advised of their new inter-donation interval by email and were also informed that appointments should be made through NHSBT’s ISAT team. The ISAT team was responsible for making this first appointment to coincide with the participant’s allocated donation frequency. For subsequent appointments during the trial, donors are given the option, and are encouraged, to make all appointments at their selected donor centre on the occasion of future donation visits.

Once randomised, donors’ participation in the trial was flagged on their donor record together with their allocated donation frequency. This flag is critical to (1) NHSBT donor centre staff, since it is essential for the booking of future appointments at the correct interval; (2) the academic coordinating centre’s helpdesk and the ISAT team, since the flag helps to identify donors’ status on the trial and resolve any queries; and (3) data management processes, such as retrieving data on donors at regular time-points from NHSBT’s donor database and securely transferring this information to the trial coordinating centre for the purposes of monitoring appointment bookings and attendance, deferrals, adverse events of donation, positive microbiology results and deaths.

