### Outcome measures

#### Primary outcome

The primary outcome is the number of blood donations made over 2 years. The number of blood donations up to (and not including) the 2-year anniversary date of recruitment will be counted.

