### Data analysis

#### Principles

Intention-to-treat analyses will be used, comparing groups as randomised. Results for men and women will be analysed separately. The principal pair-wise comparisons of groups for men will be between 10-wk and 12-wk, and between 8-wk and 12-wk intervals. For women, these comparisons will be between 14-wk and 16-wk, and between 12-wk and 16-wk intervals. For outcomes assessed at both baseline and at the 2-year follow-up, analyses of the 2-year follow-up measures will be adjusted for the baseline measures. Other baseline characteristics (age, centre, BMI and weight, SF-36v2 physical and mental component scores, haemoglobin and ferritin) will be adjusted for in secondary analyses. Tests of interaction will assess whether results differ between the subgroups pre-specified above. Multiple testing will be taken into account when interpreting these results. The trial will be reported according to CONSORT guidelines.

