#### End-of-trial analyses

The total blood collected by 2 years will be expressed in units (470 ml) per person per year. Means will be compared between groups using a t-test, with subsidiary analyses of covariance adjusting for baseline characteristics. The mean differences between groups in the PCS of the SF-36v2 will be adjusted for baseline PCS by analysis of covariance, and in secondary analyses for other baseline characteristics. Possible bias from missing data will be investigated by multiple imputation within each randomised group based on sequential additions to the imputation model: (1) baseline characteristics, (2) interim SF-12v2 scores, (3) deferral at previous blood collections, (4) number of blood collections made, and (5) number of reminders to elicit web questionnaire responses [33–35]. Other secondary outcomes will be analysed similarly. The proportion of deferrals will be analysed using logistic regression, allowing for potential over-dispersion between individuals. The baseline predictors (including genetic characteristics) of levels of haemoglobin and ferritin, and rates of deferral will be investigated using multiple (logistic) regression, employing cross-validation techniques to prevent over-fitting [36].

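### Donors who withdraw fully are asked only about data already held, so their two-year donation count may be cut short or lost although the donor database could complete it

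*Protocol article*

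**What the plan says.** All references are to the protocol article.

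- **Outcome.** Primary outcome: "The number of blood donations up to (and not including) the 2-year anniversary date of recruitment will be counted". No exception is made for donors who withdraw.
- **Analysis.** Data analysis, Principles: "Intention-to-treat analyses will be used, comparing groups as randomised". End-of-trial analyses: "Means will be compared between groups using a t-test, with subsidiary analyses of covariance adjusting for baseline characteristics".
- **Withdrawal, first step.** Ethical and safety issues: to keep as much data as possible, "participants are asked to continue to complete the trial questionnaires without donating blood".
- **Withdrawal, second step.** For those who still want to leave, "they are given the option to allow permission to the research team to retain and use data already collected from them".
- **Withdrawal, refusal.** "Participants are free to opt out of this permission".
- **Reason for withdrawal.** The same section expects that "An increase in deferrals or adverse events compared to habitual donation patterns may prompt participants to request withdrawal from the trial".
- **Data source.** Baseline data collection says the flag on the donor record supports "data management processes, such as retrieving data on donors at regular time-points" from the blood service's donor database. The stated purposes include monitoring attendance and deferrals.

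**The concern.** The outcome definition and the withdrawal rule do not fit together. The outcome needs a complete count to a fixed date for everyone randomised. The withdrawal rule, as written, secures at most the count up to the day the donor leaves. The missing part is not hard to observe, because donations are recorded in a service database and do not depend on the donor answering anything. What is missing is the permission, and no later analysis rule can recover records for which permission was never sought.

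The trial is open, and the article itself names deferrals and adverse events as reasons for leaving. Its Background gives iron deficiency and falling haemoglobin as the principal risk of more frequent donation, with deferral as a consequence. More full withdrawals in the shorter-interval arms are therefore plausible. If they occur, the comparison of total units collected rests partly on counts that are incomplete to different degrees in the arms compared.

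**Working it through.** **Inputs from the article** (Sample size calculations related to the outcomes): control mean 1.6 donations per year, SD 0.7 per year, type I error 0.05 (taken as two-sided), target increase 5%. Allocation is 1:1:1 within sex, with about 50,000 donors.

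**The article's own figure first.** The design effect is 0.05 × 1.6 = 0.08 per year. Donors needed per arm for 80% power: 2 × (1.960 + 0.842)² × 0.7² / 0.08² ≈ 1,202. Three arms need 3,606, or 7.2% of 50,000. A subgroup of 5,000 with the sexes pooled (1,667 per arm) has 91.0% power, so the stated 80% is met as a floor on that basis. This only confirms the inputs. The power figure itself is not shown in the text at hand.

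**Precision of the main comparison.** Assuming equal numbers of men and women, there are 25,000 / 3 ≈ 8,333 per arm. SE = 0.7 × √(2 / 8,333) = 0.0108 per year, and the 95% half-width is 1.96 × 0.0108 = 0.021 per year.

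**Assumptions, because the article gives no withdrawal rate.** Let *d* be the excess proportion of full withdrawals in the shorter-interval arm. Half of the two years is lost on average. The true donation rate after withdrawal, *r*, is 0.8 to 1.6 per year.

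*Path 1, truncation* (data kept, later donations not counted): bias = −*d* × 0.5 × *r*.

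| Excess full withdrawal | r = 0.8 | r = 1.6 | Share of 0.08 |
|---|---|---|---|
| 0 points | 0 | 0 | 0% |
| 2 points | −0.008 | −0.016 | 10–20% |
| 3 points | −0.012 | −0.024 | 15–30% |
| 5 points | −0.020 | −0.040 | 25–50% |
| 10 points | −0.040 | −0.080 | 50–100% |

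*Path 2, removal* (retention refused, donor drops out of the mean): bias = +*d* × *g*, where *g* is how much less withdrawers donate than stayers. With *g* = 0.4 to 0.8 per year, the sizes equal those in the table with the opposite sign. For example, 3 points gives +0.012 to +0.024, and 10 points gives +0.04 to +0.08.

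**Against the precision.** At *r* = 1.6, the excess that shifts the estimate by one 95% half-width is 0.0213 / (0.5 × 1.6) = 0.027, or about 2.7 points. The excess that cancels the design effect is 0.08 / (0.5 × 1.6) = 0.10, or 10 points. If the true effect is 0.08, a 3-point excess at *r* = 1.6 leaves power at 99.9% in the main comparison but lowers it from 91.0% to 63.7% in a pooled-sex subgroup of 5,000.

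**Is it handled elsewhere?** The multiple imputation in End-of-trial analyses follows the sentence on the physical component score, uses the number of collections as a predictor, and is extended to other secondary outcomes. It is not clearly aimed at the primary count. The allowance for one third non-completion concerns the final questionnaire only.

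**The case against.** The strongest reply is that the article is being made to say more than it does. Several parts of that reply stand.

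- **Intention-to-treat.** A reader might infer that the primary comparison is no longer intention-to-treat. The article does not support this. Principles fixes analysis as randomised, and nothing excludes withdrawers or moves them between arms. Counts lost through withdrawn consent are missing outcomes within such an analysis.
- **Arm-dependence.** A reader might take differential withdrawal as established. It is plausible from the article's own sentence, but no rate is given, overall or by arm.
- **Scale.** Donors who accept the questionnaires-only step remain countable, so only those who go beyond it are affected. A donor who merely gives blood less often than allocated, and stays in the trial, is also fully counted.
- **Later donation rate.** The Background notes that deferral may discourage future donation, so 1.6 per year after withdrawal is probably an upper value.
- **Harm signal.** A reader might infer that deferrals vanish from the safety picture. A deferral that prompts withdrawal precedes it, so it is already collected and is kept unless the donor refuses. The monitoring committee also reviews safety data at least every six months.
- **Consent.** The right to refuse use of data is not a statistical error, and some loss would remain under any rule.

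It is also true that the article nowhere says database extraction stops at withdrawal, and a full protocol or analysis plan may say how withdrawers are counted. That answers only part of the point. The withdrawal permission is stated here, and as stated it covers existing data only.

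**Conclusion.** The point stands in modest form. Taken literally, the withdrawal rule cuts short or loses primary-outcome counts that the donor database could complete. It is worth fixing because the remedy is cheap.

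No size can be read off the article. Under the assumptions shown (2 to 10 points more full withdrawal in the shorter-interval arm, half of follow-up lost, later donation at 0.8 to 1.6 per year), truncation alone moves the estimate against the shorter interval by 0.008 to 0.08 per year. Removal of low donors moves it in favour by similar amounts. The mix of the two is unknown, so a claim that the trial is biased in one particular direction would not be supported. With equal withdrawal of similar donors, or with complete database counts for everyone randomised, the bias is about zero. The trial's size does not protect against this: with a half-width of about 0.021 per year, a small systematic shift would be estimated precisely.

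**What to change.** From now on, record three separate choices at withdrawal: leaving the allocated interval, stopping questionnaires, and refusing passive record linkage. This concerns data permissions only, not when anyone may donate.

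1. Ask each withdrawing donor for permission to keep drawing dated donation and deferral records from the blood service's database up to the two-year anniversary.
2. In the primary analysis, count all such donations in the arm randomised.
3. Report full withdrawals, refusals of linkage and refusals of data retention by arm and sex.
4. Add a sensitivity analysis for counts that remain missing, using the five-year donation and deferral history retrieved at baseline where the donor allows its use.

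**Cost.** An ethics amendment to the withdrawal form and script, for which Trial oversight describes the route, and continued use of an existing data extract. No new visits are needed. Some donors will still refuse. The change is prospective: recruitment ran from June 2012 to June 2014, so the earliest participants were reaching two years as it closed, and donors who have already withdrawn are not covered unless they are re-contacted.

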### Patient and public involvement

Donors have been involved in the design and undertaking of the INTERVAL trial in several ways, such as through (1) provision of feedback during the pilot study preceding this trial (that is, the Cambridge CardioResource Study) via questionnaires, interviews, and helpline services; (2) review of research proposals and questionnaires; and (3) membership on the Trial Steering Committee.

### Trial oversight

In addition to the Independent Data Monitoring Committee and the Research Ethics Committee mentioned above, INTERVAL benefits from the input of other trial oversight committees. The Trial Steering Committee (which includes several senior clinical and academic members who are independent from the trial investigators, a lay representative, and representatives of various stakeholders in INTERVAL) monitors the overall conduct of the trial and, through its independent Chair, provides strategic advice to the Trial Management Group. The Trial Management Group (which includes the investigators, trial coordinators, and operational staff from NHSBT) is responsible for overseeing day-to-day management of the study, liaising with NHSBT, and agreeing protocol amendments prior to submission to the research ethics committee.

## Discussion

To our knowledge, there are no previous or planned randomised trials in the UK or elsewhere that aim to define optimum inter-donation intervals and/or tailor such intervals to particular groups of blood donors. Although some randomised trials have been conducted or are in progress to evaluate the impact of oral iron supplementation [37, 38], they are complementary to INTERVAL and evaluate populations outside the UK. The INTERVAL randomised trial is also complementary to recent major observational studies reported in blood donors, such as those in the US [39] and in continental Europe [40].

In summary, the experience so far of the INTERVAL trial suggests that it is possible to embed large-scale clinical research within NHSBT without disruption to routine services, and in a manner that is acceptable to donors. The INTERVAL trial will yield novel information about the effect of inter-donation intervals on donors’ physical and mental well-being as well as on blood services. The study will generate scientific evidence to help formulate blood collection policies in England and elsewhere.

## Trial status

Recruitment in INTERVAL was completed on 15 June 2014.

## Abbreviations

AEs: adverse events
BMI: body mass index
DNA: deoxyribonucleic acid
EDTA: ethylenediaminetetraacetic acid
HFE: human haemochromatosis gene
ID: identification
ISAT: INTERVAL study administration team
NHS: National Health Service
NHSBT: NHS Blood and Transplant
PCS: Physical Component Score
RPAQ: Recent Physical Activity Questionnaire
REC: research ethics committee
SAEs: serious adverse events
SF-12v2: Medical Outcomes Study 12-item Short-Form Health Survey, version 2
SF-36v2: Medical Outcomes Study 36-item Short-Form Health Survey, version 2
URL: uniform resource locator link.
